**Strategies for the management of trachomatous trichiasis**

**Trial 2: Randomised controlled trial of epilation against surgery for management of minor trachomatous trichiasis**

**Study Protocol**

**Summary**

Trachoma is the leading infectious cause of blindness worldwide. Chronic keratoconjunctivitis caused by Chlamydia trachomatis causes scarring of the inner eyelid. This in turn causes in-turning of the eyelid (entropion), causing the eyelashes to turn inwards (trichiasis) and rub the cornea, resulting in scarring and visual impediment. SAFE is the WHO initiative for the control of trachoma. It comprises, Surgery, Antibiotics, Facial cleanliness and Environmental improvement. The surgery aims to correct the trichiasis, thereby preventing further visual loss. However surgery can have a high recurrence rate. It is unknown whether surgery should be carried out on all degrees of severity of trachomatous trichiasis or whether epilation should be practised in less severe case. This trial aims to determine if epilation is non-inferior for minor (5 or less eyelashes touching the globe) trichiasis.

**Trial Location and format**

The trials are planned to be undertaken in the West Gojjom zone, Amhara region.

Trachomatous trichiasis surgical campaigns will be organised in several health centres and/or health posts. Recruitment will take place during these campaigns.

**A: Trial Recruitment Phase (see diagram 1 below)**

1. **Identify locations (see diagram 2 below) for different parts of recruitment process**

Team Members who will perform this (appendix A)

SR (research fellow) and nurse 1 (examination nurse)

1. **Presentation to patients and accompanying people**

Team Members

Assistants 1 and 2 (consent field workers)

Procedure

- 1. Hand out project information sheets.
  2. Introduction re who we are.
  3. Info about what is known about trachoma.
  4. Info about what is not known about trachoma.
  5. Info about the trials.
  6. Info about safety to patient.
  7. Info about what we will do from now.

Late comers will receive similar presentation individually or in small groups.

1. **Triage Patient**

Team members

Field worker to call SR or EM to triage Patient to:

- 1. Trial 1 or trial 2
  2. Treatment for right eye/left eye/bilateral
  3. Decide which is trial eye if bilateral TT (using random eye table)

Procedure

1. Patients with trachomatous eye disease and no exclusion criteria, enter into study.
2. Patients with trachomatous eye disease and exclusion criteria. Do not enter into study, but give standard trachoma treatment, including surgery if required.
3. Patients with non-trachomatous eye disease:
   - 1. Emergency: to be seen by ophthalmologist or ophthalmological nurse and treated if necessary or arrangements made for urgent referral to local eye facility
     2. Non-emergency: to be seen by ophthalmological nurse and instructions for attendance at local eye unit with referral letter if required.

Inclusion criteria – trial 1

Patients with major trachomatous trichiasis (greater than 5 eyelashes touching the globe of either or both eyes), who consent to be part of the trial and do not have any of the exclusion criteria below.

Inclusion criteria – trial 2

Patients with minor trachomatous trichiasis (5 or less eyelashes touching the globe of either or both eyes), who consent to be part of the trial and do not have any of the exclusion criteria below.

Exclusion criteria for both trials

- Age less than 18 years
- Previous eyelid surgery
- Medically unfit, BP systolic >170, diastolic >110.
- Pregnant

1. **Consent**

Team Members

Assistants 1 and 2 (Consent field workers)

Procedure

- 1. Check if they heard initial lecture and if so whether they understood it.
  2. If not, then explain trachoma/trial.

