**Appendix B – Questionnaire and examination protocol and study record form**

**Patient Examination**

1. **General Examination**
   1. **Height in centimetres**
   2. **Weight in kilograms**
   3. **Determine trial eye**

Use pre-designed random eye table

- 1. **Record eye being treated**

1. **Ophthalmic Examination**
   1. **Visual Acuity:**  **EDTRS tumbling E logmar chart at 4m**

a) Best corrected

b) Pinhole vision

To calculate LogMAR visual acuity for 4m:

1. Test to lowest line on which any letter can be read. Complete whole line, even if many mistakes.

2. Take the LogMAR score for the lowest complete line read

3. Add 0.02 x n to this score, where n = the number of letters read from the non-completed line.

N.B

If chart is read at 2m: add 0.3 correction

If chart is read at 1m: add 0.6 correction

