**Studies on the Management of Trachomatous Trichiasis**

**Analytical Plan for Trial 2: Randomized controlled trial of immediate surgery vs. epilation for Minor Trichiasis**

**1. Participant flow**

*a) Eligibility, enrolment and follow-up*

The following will be shown by trial arm in a flowchart following CONSORT guidelines for non-inferiority trials (JAMA 2006: 295:1152-1160): Numbers eligible, consenting to take part, randomized, and who received the intended treatment. The numbers still in follow-up, censored, defaulting, and permanently lost-to-follow-up respectively at each visit will also be shown by arm. Reasons for declining to take part, not having surgery, or discontinuing follow-up will be summarized by arm.

*b) Censoring*

Patients in both arms will be considered as failures and immediately censored when they present with 5+ lashes in the trial eye. In addition, patients who present having had surgery (or repeat surgery) on the trial eye from other providers will be considered as failures and immediately censored.

1. **Description of baseline data**

The following characteristics of participants at baseline will be tabulated by arm:

- 1. Socio-demographic factors: age, sex, literacy, ethnic group.
  2. Behavioural factors: epilation habits, whether surgery has previously been offered, reasons for not having surgical treatment previously.
  3. Clinical status: trichiasis, entropion, inflammation, conjunctivilisation of lid margin, corneal scarring, evidence of epilation, visual acuity, symblepharon.

The distributions of these variables by treatment arm will be compared, to assess whether there is imbalance at baseline in these potential confounding factors.

1. **Primary outcome**

*a) Definition*

The primary outcome measure will be the proportion of participants with 5 or more lashes touching the eye on one or more follow-up visits. Lids with eyelash stubs which are not in contact with the eye will not be considered a treatment failure.

*b) Justification of primary outcome measure*

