Trichiasis (lashes touching the eyeball) causes visual loss through corneal opacification. The purpose of the interventions being compared in this trial is to stop eyelashes touching the eyeball. It is anticipated that some of the patients in the surgery arm of the trial may commence epilation if their surgery fails. From an ophthalmic public health perspective they are ‘successes’ if they successfully prevent eyelashes touching the globe, despite the surgery itself having not been totally successful.

Previous studies have used a cut-off of 5 or more lashes for determining treatment choices (Arch Ophth 2006; 124: 309-314). Similarly, this level has been used in national blindness control programmes (The Gambia) as an indication for surgery.

*c) Sample size*

Our sample size of 1300 trial participants would provide 90% power to detect non-inferiority, assuming 10% loss to follow-up over 2 years, a 5% failure rate in the surgery arm, and non-inferiority margin of 10%. (i.e we would conclude non-inferiority if the upper 95%CI for the observed difference in failure rates was less than 10%)

The power to detect non-inferiority under different assumptions with this sample size is shown in the table below

**Table 1:** Power for detecting non-inferiority under different assumptions with sample size of 585 per arm (1300 recruited, 10% loss to follow-up)

| **Proportion failing in surgery arm (**[figure not shown] | **Proportion failing in epilation arm (**[figure not shown] | **Difference in proportions (**µ) | **Inferiority margin (**Δ) | **Power** |
| --- | --- | --- | --- | --- |
| 2% | 6% | 4% | 8% | 93% |
| 2% | 8% | 6% | 10% | 89% |
| 3% | 6% | 3% | 8% | 98% |
| 3% | 9% | 6% | 10% | 85% |
| 4% | 8% | 4% | 8% | 82% |
| 4% | 8% | 4% | 10% | 99% |
| 4% | 9% | 5% | 10% | 94% |
| 5% | 9% | 4% | 8% | 76% |
| **5%** | **10%** | **5%** | **10%** | **90%** |
| 8% | 11% | 3% | 8% | 83% |
| 8% | 12% | 4% | 10% | 93% |

*d) Statistical analysis*

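### Trial 2's lash criterion applies to the person and its outcome to one trial eye, so an eye with more than 5 lashes can become the trial eye

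*Protocol*

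**What the plan says.** The Protocol summary limits the question to minor trichiasis, meaning no more than 5 lashes touching the globe. Section A (Triage Patient) gives the two lash criteria:

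- Trial 1: "greater than 5 eyelashes touching the globe of either or both eyes"
- Trial 2: "5 or less eyelashes touching the globe of either or both eyes"

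The same section has triage assign the patient to one of the two trials and then gives the trial-eye rule: "Decide which is trial eye if bilateral TT (using random eye table". Appendix B (General Examination) repeats it as "Use pre-designed random eye table". Neither place sets a lash condition on the eye drawn.

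The Analytical Plan defines the primary outcome as "the proportion of participants with 5 or more lashes touching the eye on one or more follow-up visits". Its censoring rule refers to the single eye: "Patients in both arms will be considered as failures and immediately censored when they present with 5+ lashes in the trial eye". The primary analysis is a modified intention-to-treat analysis of everyone seen at least once.

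**The concern.** Eligibility is judged over two eyes and the outcome in one. Take a person with 3 lashes touching in one eye and 8 in the other. They satisfy both criteria, so two triage staff could place them in different trials and both be following the text. If they enter Trial 2, nothing written stops the 8-lash eye from becoming the trial eye.

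Such an eye belongs to the question Trial 1 addresses. In Trial 2 it would add failure rates from a different severity range to both arms. The non-inferiority conclusion would then apply to a mixture of minor eyes and an unstated number of major ones.

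**Working it through.** **Step 1: can a major eye be the trial eye?** Follow the 3-and-8 person through the text.

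| Stage | Rule | Result |
|---|---|---|
| Trial 1 criterion | more than 5 lashes in one or both eyes | met by the 8-lash eye |
| Trial 2 criterion | 5 or fewer lashes in one or both eyes | met by the 3-lash eye |
| Exclusion list | age, previous lid surgery, medical fitness and blood pressure, pregnancy | does not cover eyes of differing severity |
| Choice of trial | Trial 1 or Trial 2 at triage; diagram 1 adds no rule | not determined |
| Choice of trial eye | random eye table for bilateral disease | either eye |
| Primary analysis | everyone seen at least once | the eye stays in |

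The planned subgroup analyses are by entropion and conjunctivilisation. Neither separates out eyes by baseline lash count.

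**Step 2: is that eye a failure at entry?** No. Failure needs 5 or more lashes at a follow-up visit, and surgery or epilation starts after the baseline count. An 8-lash eye with fewer than 5 lashes touching at every visit attended, and no surgery on it from another provider, is a success. It starts above the failure count and no more than that.

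**Step 3: does it bias the arms?** Triage and the choice of trial eye come before the envelope is opened (section A; Appendix C). Major trial eyes are therefore split between arms by chance.

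**Step 4: the plan's own power.** Inputs from the sample size section and Table 1: 585 analysed per arm, failure 5% with surgery and 10% with epilation, margin 10 points, one-sided alpha 0.025.

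Power = Φ((margin − difference)/SE − 1.96), with SE = √(p_S(1−p_S)/n + p_E(1−p_E)/n).

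SE = √(0.05×0.95/585 + 0.10×0.90/585) = 0.01533. (0.10 − 0.05)/0.01533 − 1.96 = 1.30. Power = 90.3%, which reproduces the stated 90%.

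**Step 5: illustration with major trial eyes.** Let a share f of trial eyes be major, failing at q_S with surgery and q_E with epilation. Then p_S = f·q_S + (1−f)·0.05 and p_E = f·q_E + (1−f)·0.10. The values of f, q_S and q_E are all assumed; the documents give none of them.

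| Assumed failure in major eyes (surgery / epilation) | f = 2%: difference, power | f = 5%: difference, power | f = 10%: difference, power |
|---|---|---|---|
| 15% / 40% | 5.4 points, 83% | 6.0 points, 69% | 7.0 points, 42% |
| 15% / 30% | 5.2 points, 87% | 5.5 points, 80% | 6.0 points, 67% |
| 15% / 15% | 4.9 points, 91% | 4.75 points, 92% | 4.5 points, 93% |
| 30% / 15% | 4.6 points, 93% | 4.0 points, 96% | 3.0 points, 99% |
| 100% / 100% | 4.9 points, 85% | 4.75 points, 79% | 4.5 points, 71% |

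Worked cell (15%/40%, f = 10%): p_S = 0.015 + 0.045 = 0.060; p_E = 0.040 + 0.090 = 0.130; SE = 0.0170; (0.10 − 0.07)/SE − 1.96 = −0.20; power 42%.

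**Step 6: how little movement matters.** Table 2 assumes 8% overall failure. A 6-point difference has an upper limit of 9.1% and is called non-inferior. A 7-point difference has 10.1% and is called borderline. One point separates the two conclusions.

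**The case against.** The strongest reply is that the criteria open by naming patients with major or minor trichiasis. The words about one or both eyes may only mean that unilateral and bilateral disease both qualify. On that reading anyone with a major eye is a major patient and goes to Trial 1. Triage is done by the research fellow or a named colleague, the choice of trial is listed before the choice of eye, and the eye table itself is not shown. This reading is plausible, so the entry of major eyes is possible and not demonstrated. But it is not written down, and it sits badly with a Trial 2 criterion that one qualifying eye can satisfy.

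A reader might infer that a major trial eye begins the trial as a failure. The documents do not support this, because the outcome is assessed only at follow-up visits. Nor is starting at the failure count peculiar to major eyes: an eye with exactly 5 lashes is eligible and already at it. That shared boundary is a separate matter.

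A reader might also infer that the arms become incomparable, or that power certainly falls. The first fails because the draw precedes randomisation. The second fails because the direction depends on how each treatment performs in major eyes. The most damaging cell (42%) also implies overall failure of (6% + 13%)/2 = 9.5%, against the 8% that the Analytical Plan reports from blinded data. With the base rates also assumed this is not decisive, but it lends that cell no support.

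Finally, exclusion is not the only remedy at analysis. Lash counts are recorded for each eye, so stratifying or adjusting by baseline count is also open.

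**Conclusion.** The point holds as a defect in the eligibility and trial-eye rules. As written, a person with one eye above 5 lashes and the other at 1 to 5 qualifies for both trials, no rule chooses between them, and the major eye can become the Trial 2 trial eye and stay in the primary analysis. The consequence is a population wider than the stated question, with altered failure rates and power. It is not a biased comparison between arms.

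The size cannot be fixed. The illustrations run from 42% to 99% power at a 10% share, and from 83% to 93% at 2%. They rest on assumed shares and assumed failure rates in major eyes, on 5% and 10% failure in the remaining eyes, and on a normal approximation with 585 per arm. If no major eye was drawn, nothing changes except the wording. The change is worth making because the remedy is cheap and determines which eyes the conclusion covers.

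**What to change.** For the criteria and any reuse of this protocol:

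1. State that the Trial 2 trial eye must itself have 5 or fewer lashes touching at baseline.
2. Restrict the random-eye draw, in section A and in Appendix B, to eyes that meet that criterion.
3. State which trial a person with one minor and one major eye enters.

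For this trial: the Analytical Plan refers to blinded analyses done at its end, so recruitment is presumably over. Report by arm the number of trial eyes with more than 5 lashes touching at baseline, and repeat the primary analysis without them. The exclusion uses a count taken before randomisation, so it leaves the randomised comparison intact. If the count is zero, one sentence saying so closes the point.

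Cost: a few lines of protocol text, and one count plus one sensitivity analysis. The study record form already holds medial, lateral and corneal lash counts for each eye, so no new data are needed.

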   1. Take 3 (if unilateral surgery required) or 6 (if bilateral) silk sutures from the suture store and give to the surgeon. They will ask the surgeon to double check that this is the correct (silk) suture.
   2. They will use masterlist E3 (see below) to record whether the patient needs suture removal to be performed in 7-10 days. This will be recorded on two copies of masterlist E3.

Master list E2

| Date | Study Number | Name | Randomisation Envelope | Study Eye | Treatment given |
| --- | --- | --- | --- | --- | --- |
|  | 1 | XX | E1/0001 |  | E |
|  | 2 | Xx | E2/0001 |  | S |
|  | 3 | Xx | E3/0001 |  | E |
|  | 4 | Xx | E1/0002 |  | E |
|  | 5 | Xx | E3/0002 |  | S |
|  | 6 | Xx | E2/0002 |  | S |

Masterlist E3 – suture removal

| Unique identifier | Name | Date of surgery | Date for suture removal | Eye for suture removal (R/L/B) | Sutures successfully removed  (yes or no) |
| --- | --- | --- | --- | --- | --- |
|  |  |  |  |  |  |
|  |  |  |  |  |  |
|  |  |  |  |  |  |

1. **(a) Surgery**

Team Members

Nurses 2, 3 and 4 (surgical nurses), assistant 7 (surgical assistant). Up to five different surgical nurses will be involved in operating patients in the trial, although unlikely to be more than three nurses working on the same day.

Procedure

- 1. Nurse 2, 3 or 4 to operate on patient
  2. Nurse 2, 3 or 4 will record the surgical outcome on masterlist E4 (see below)
  3. Nurse 2, 3 or 4 to give post-op instructions
     1. Tetracycline
     2. Keep eye clean
     3. Not to rub eye
     4. Return 7-10 days for removal of silk (BLACK) sutures and recording of immediate post-op complications

The Trabut surgical technique will be used (appendix D)

Sterilization will be as per The Trichiasis Surgery for Trachoma WHO manual (appendix E)

All sharps (needles, blades etc) will be disposed of in specialised ‘sharps bins’

Masterlist E4

| Unique identifier | Name | Date of surgery | Surgery routine or complicated | Complication (if applicable) |
| --- | --- | --- | --- | --- |
|  |  |  |  |  |
|  |  |  |  |  |
|  |  |  |  |  |

Procedure to follow if intra-operative complication

- Follow local policy
- However, ensure that same suture as was initially randomised is still used, even if more or less than usual are needed.
- Masterlist S4 (see above) will be used to record any intra-operative complications.

**(b) Epilation training**

Team Members

Assistant 8 (epilation field worker)

Procedure

*A. If patient and suitable relative both present at surgical camp*

1. Take patient and relative to designated epilation training area.
2. Re-explain purpose of trial
3. Explain need for:
   1. Good quality epilation
   2. Regularity of epilation
4. Test near vision of relative.
5. Show forceps to relative and ask if they have epilated previously.
6. Warn of hazards of forceps:
   1. Corneal trauma
   2. Breaking lashes to leave abrasive stubs
   3. Remind that there is a contact number on the information sheet if difficulties do arise and give named person to contact in case of concerns.
7. Tell relative of need for good lighting and undisturbed location.
8. Observe relative epilating.
9. Check lid after epilation:
   1. If epilation fully successful (no trichiatic lashes remain): give epilation pack as per (10)
   2. If epilation partially successful (no lashes touching globe/cornea, but trichiatic lashes remain) (i.e. give advice.
   3. If epilation failed (lashes touching globe/cornea):
      1. Either: repeat full epilation training
      2. Or: ask if another more appropriate relative is available

But do NOT exclude from trial.

1. Give epilation pack:
   1. Forceps
   2. Lid diagram/diary cards in A4 plastic wallet.
   3. Pencil

*B. If patient not with suitable relative*

1. Investigate if suitable relative can be found: consider:
   1. Either: Deferring epilation training until later in the week
   2. Or: project driver to fetch relative.

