**B: Trial Follow-up Phase**

1. **7-10 day follow-up for surgical patients**

Team members

Nurse

Driver 2, if patient fails to attend for follow up

1. Find appropriate patients according to suture removal lists from each trial.
2. Record post operative examination on new form for patient
3. Double check that this patient is from trial 2 and therefore has silk (BLACK) sutures.
4. Remove all sutures.
5. Record removal of sutures on masterlist E5
6. Give patient further instructions

Masterlist E5

| Unique identifier | Name | Date of suture removal | Eye of suture removal | Early post operative findings |
| --- | --- | --- | --- | --- |
|  |  |  |  |  |
|  |  |  |  |  |
|  |  |  |  |  |

Examination

1. Are/is there:
   1. Discharge
      1. Purulent
      2. Non-purulent
   2. Obvious granuloma (do NOT evert lid)
   3. Bleeding
   4. Early recurrence
      1. Count eyelashes and record
   5. Skin infection / cellulitis
2. Is further surgery being planned?
   1. When?
   2. Where?

Procedure if early recurrence is identified

Either:

1. Operate immediately, if suitably trained surgeon is present
2. Refer to Bahir Dar for urgent re-op
3. Refer to another local surgical campaign, if there is capacity and a suitably trained surgeon.

Failure to present at 7-10 follow up

1. Is this due to:
   1. Death
   2. Travelled
   3. Unknown
2. Driver and suture removal nurse to take all possible steps to find patient or arrange for their presentation as soon as possible for suture removal.

Late complications

If patient re-presents between the 7-10 day follow up and the 3 month follow up, record reason and presence/absence of any of the above complications and follow procedure above.

1. **6 month follow up**

Team

Field Co-ordinator with SR assistance

Driver 1

Assistants

Aims

Full examination and photography

Swabs

1. **One year follow up**

Team

SR

Field co-ordinator

Assistants

Driver 1

Aims

Full examination and photography

Questionnaire

Visual acuity

Swabs

1. **18 month follow up**

Team

Field co-ordinator with SR assistance

Driver 1

Assistants

Aims

Full examination and photography

Swabs

1. **Two year follow up**

Team

SR

Field co-ordinator

Assistants

Driver 1

Aims

Full examination and photography

Swabs

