**Appendix F – Diagrammatic Representation of Corneal Scar Grading**

**Appendix G:**

**Data Safety Monitoring Committee – terms of reference:**

A Data Safety Monitoring Committee (DSMC) will be responsible for monitoring the safety of this trial.

***Specific terms of reference****:*

1. Protect the safety of the study participants.
2. Review research protocol and trial documentation.
3. To determine if an interim analysis of trial data should be undertaken.
4. To determine what should be reported to the DSMC as a serious adverse event (SAE).
5. To consider the data from interim analyses (if deemed necessary), unblinded if considered appropriate, plus any additional safety issues for the trial and relevant information from other sources.
6. In the light of 5., to report to make recommendations to the Trial Steering Committee regarding modifications or continuation of the trial.

***Membership****:*

There will be 3 members, all independent of the running of the trial with relevant clinical and epidemiological experience. They will be appointed by the PI.

***Meeting schedule****:*

The DSMC will determine their specific meeting arrangements. It is proposed that the DSMC would meet prior to the beginning of the trial, half way through (one year) and at the end (two years).

***Quorum****:*

2 members

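### Structured harm recording covers the surgical arm only, and no item shown captures the two epilation hazards that the protocol itself names

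*Protocol*

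**What the plan says.** **Epilation arm.** Protocol section (b) Epilation training has the field worker warn the relative of "Corneal trauma" and of "Breaking lashes to leave abrasive stubs". If problems occur later, the instruction is: "Remind that there is a contact number on the information sheet if difficulties do arise". A named person is also given. No log or form is stated for what is then reported.

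**Surgical arm.** In section B, Trial Follow-up Phase, the early complication check stands under the heading "7-10 day follow-up for surgical patients". Its Late complications paragraph says that, when a patient comes back before the 3 month follow-up, staff are to "record reason and presence/absence of any of the above complications and follow procedure above". The complications meant are those of the post-operative list.

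**Outcomes.** The Analytical Plan (Primary outcome, a) Definition) states: "Lids with eyelash stubs which are not in contact with the eye will not be considered a treatment failure". Its secondary outcome on complications is confined to the surgical arm.

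**Oversight.** Appendix G gives the safety committee (DSMC) as its first task: "Protect the safety of the study participants".

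**The concern.** The trial asks whether epilation, done at home by a relative, may stand in for surgery. A finding of non-inferiority on lashes touching the eye will be read together with the harms of each treatment. That reading is fair only if harms are looked for in a comparable way in both arms.

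Here one arm has prompts, lists and an outcome for its harms. The other has a warning, a telephone number and general examination items. A field that was never on a form cannot be supplied later by an analysis plan, so this has to be settled in the protocol and its forms.

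**Working it through.** The plan gives no figure on this point, so the check sets the sections side by side.

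**1. Where harm is recorded, by arm**

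| Stage | Surgery | Epilation |
|---|---|---|
| Day of treatment | Complications on masterlist E4 (section A, Surgery) and in the E3 logbook (Appendix C) | Lid checked after the observed epilation; no form named |
| Days 7-10 | Visit with a list (discharge, granuloma, bleeding, early recurrence, skin infection), entered on E5 | No visit |
| From then to 3 months | Unscheduled return: reason and complications recorded | Contact number and named person; no record stated |
| 6, 12, 18, 24 months | Full examination with photographs | The same |
| Outcome | Risk of complications at one and two years | No counterpart; a question on whether epilating is painful |

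The arms are treated alike from month 6 on. The imbalance lies in the period before that and in the outcome list. After training, the first scheduled contact of an epilation patient is at month 6.

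**2. What the common examination can detect (Appendix B)**

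- *Cornea.* Scarring is graded and photographed, and each opacity is photo-graded for size and density. This captures lasting opacity. A fresh abrasion has no item. The Analytical Plan's footnote on corneal opacification accepts that examination can miss small changes and that opacity has other causes, trauma among them. The scar grade therefore neither detects a healed abrasion nor attributes a scar to forceps.
- *Stubs.* Epilation is graded for presence, extent and success, and success is expressed by number of lashes. Stubs are not named.
- *Other.* There is a free-text notes field, which is unprompted.

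**3. Stubs and the primary outcome**

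The failure definition exempts stubs clear of the eye, so the examiner has to judge whether a stub touches. No field shown records that judgement. Appendix B counts lashes by whether their point touches; that a touching stub counts as a lash is implied, not stated.

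**4. What is compared between arms (Analytical Plan, Secondary outcomes)**

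Change in corneal opacity to 24 months, visual acuity at 12 and 24 months, and eye pain and watering at 12 months are compared by arm. Lasting or symptomatic damage can therefore enter the results. A stub, or an abrasion that has healed by the visit, has no dedicated route.

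**5. Route to the safety committee (Appendix G)**

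The committee decides what counts as a serious adverse event, what data it needs and how reporting works. None of this is limited by arm. The route for epilation harms is unspecified, not closed.

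**The case against.** Several stronger readings are tempting, and the documents do not support them.

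- *Epilation harms cannot appear in the results.* A reader might infer this from the missing items. But all four later visits prescribe the full examination and photographs without restriction by arm, and opacity, acuity and pain are compared by arm. Lasting corneal harm would be visible.
- *Such harms cannot reach the safety committee.* The committee's terms are open to any safety issue in either arm and let it request what it wants.
- *The forms contain no such item.* Only the baseline record form is shown. The Analytical Plan cites follow-up questionnaires with questions that are absent from it, so other instruments exist. Epilation patients also receive lid diagrams and diary cards whose content is not described. A follow-up item cannot be ruled out.
- *Returns are recorded unequally for two years.* The surgical rule ends at 3 months. After that neither arm has one.
- *The number of missed events can be calculated.* It would need an assumed risk and the assumption that nothing else captures any event. The documents support neither.

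It can also be said that a yes/no field at six-monthly visits will miss most short-lived abrasions and could itself look falsely reassuring. That is fair, and it limits how the data may be reported. It does not remove the case for recording stubs or for logging early returns in both arms.

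What remains after these points is the unequal structure: prompted recording, a return rule and an outcome for surgery, and none of the three for the hazards the protocol names for epilation.

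**Conclusion.** The point holds in a limited form. In the text shown, harm ascertainment is unbalanced by design, mainly before month 6 and in the list of outcomes. Acute or transient harm from epilation may be under-recorded. Lasting corneal damage, loss of acuity and pain are covered in both arms.

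No size can be given, because the protocol states no risk of corneal injury or stubs under epilation. The non-inferiority calculation is not affected. What is affected is how far a favourable result can be presented together with a balanced account of harms.

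The conclusion assumes that the follow-up forms and diary cards not shown do not already collect these items. If they do, what remains is the return rule and the one-sided complications outcome. This is an inexpensive improvement worth making, not a flaw that undermines the trial.

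**What to change.** 1. At the 6, 12, 18 and 24 month examinations in both arms, record for the trial eye the number of broken lashes or stubs, split into touching and not touching the eye, and visible corneal injury (yes/no). Omit this if the follow-up forms already do so. The split also documents the judgement that the failure definition requires.
2. Move the recording part of the unscheduled-return rule out of the surgical section so that it applies to both arms: date, reason and findings, including the two new items. Only recording changes; clinical management stays as written. State the end of the window as well, since the rule refers to a 3 month follow-up that the visit schedule does not list.
3. Tabulate these items by arm for the DSMC and in the final report, beside the surgical complications.

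The cost is two fields on a form for an examination already planned, and one rule widened. The forms become slightly longer; no visit, staff or test is added. Injuries that heal between visits will still be missed, so the report should say that a low count is not evidence of no harm.

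The Analytical Plan mentions blinded analyses done at the end of the trial. If visits are already complete, the stored lid and corneal photographs could be re-read for stubs and corneal damage in both arms, and the unequal recording stated as a limitation.
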